#### Controlled group

Controlled arm will correspond to standard medical strategy for assessing consumptions while prescribing OMT. Excluding OS-UDS, there will be no prohibited procedure. In particular, GPs of the controlled harm are authorized to implement any biological test to ascertain associated substances use, including for instance laboratory testing. However, according to previous data, we can expected that few drug tests should be performed in this control group: 1 to 3 % [11, 27].

### Outcome measures

The primary outcome will be OMT retention at 6 months. Secondary outcomes will be patient adherence to buprenorphine, associated psychoactive substances use, acceptability of OS-UDS reported by the patient, acceptability of OS-UDS reported by the GP.

#### Primary outcome

Retention in treatment at 6 months will be the main judgment criterion. Actually, a review on all Cochrane systematic reviews performed by the Cochrane Review Group on Drugs and Alcohol highlighted that the main outcomes used in studies assessing effectiveness of opiate maintenance treatment were retention in treatment and illicit use of heroin [4]. Whatever the treatments compared, the retention in treatment was the most constant and the most reproducible outcome used over the different clinical trials because heroin use (assessed through different ways, self-reported or through urinary analysis) is rarely reported in a standardized way. This outcome could be considered as intermediate steps of treatment for heroin-addicted patients. Because observational studies showed high rates of mortality in heroin-addicted patients [37], especially early after discharge from treatment, the ability of a treatment in retaining people in treatment should be reported as a proxy of effectiveness [38].

Retention in treatment will be defined as patients remaining under opiate maintenance treatment at 6 months in a context of medical care (i.e. drug prescribed by a physician, not diverted or obtained through an illegal way, whatever the drug considered, buprenorphine; buprenorphine/naloxone, methadone) and assessed by the general practitioner at the end of the follow-up. Patients switching from buprenorphine to methadone or to buprenorphine/naloxone during study follow-up will be considered as remaining under opiate maintenance treatment.

The patient will be defined as retained in treatment if he will be prescribed by the same GP a legal opiate maintenance drug, or if the drug will be prescribed by another practitioner in connection with the treating physician. In case of loss of follow-up or diverted use of drug (intravenous or nasal route or illegal acquisition of the OMT drug), the patient will be considered as not retained. In case of death, the patient will be considered as maintained until the date of death, and censored after this date. Buprenorphine must be prescribed under strict conditions for a maximum of 28 days (methadone for a maximum of 14 days). Consequently, a patient not attending a medical visit for more than 56 days (2 months) should be considered as not remaining under opiate maintenance treatment.

Retention in treatment has to be recorded at 6 months (time window tolerated of +/− 14 days) as there is no scheduled or mandatory visit for the patient.

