### Intervention

Intervention will consist in: 1) a training session for GPs on use and interpretation of OS-UDS; 2) the supply of OS-UDS at GPs’ medical offices; 3) performing an OS-UDS before the first prescription of buprenorphine. GPs will be let free to perform OS-UDS for the follow-up if they judge it necessary.

GP assigned to the intervention group will be visited by a clinical research assistant (CRA) to be trained on the methods for performing test (urinary sample collection and reading of the test results). The training session is expected to last about 1 h, and a written guidance will be provided. Material for testing (OS-UDS) will also be supplied during this session. OS-UDSs will be centrally bought by the CHU de Toulouse and will be provided by the CRA in charge of the training session.

During the consult, GPs of the intervention group will dedicate an average 5 min to perform OS-UDS. Patients will be asked to collect a urine sample at the GP’s medical office. GP will read and communicate the results immediately to the patients. GPs will keep free of their management according to OS-UDS results.

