#### Cross-link data

To ensure completeness in prescription drug records, significant medical event and death occurring during follow up, additional information on medical care will also be obtained through the database of the health insurance scheme. A query into the information system from the national health insurance scheme database (SNIIRAM) and national mortality registry will be done to complete follow-up [39]. Patients will be matched thanks to a probabilistic match [40]. In a recent study, around 80 % of patients had been matched between general practice data and health insurance scheme data [41]. Data collected will not be included in the main analysis.

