### Sample size calculation

Comparisons between groups will be performed taking into account clustering which the unity will be the GP. Thus the sample size must be corrected by an inflation factor according to guidelines on clustered analyses [42–45]. According to the results of a previous study performed by our group on patients initiating buprenorphine in ambulatory care in the Midi-Pyrénées area [27], we were able to identify clusters of GPs and calculated the intra-cluster correlation coefficient (CCI = 2.79 %) and the mean cluster size (m = 2), giving an inflation factor (IF = 1.03).

According to the literature, the retention rate with buprenorphine at 6 months is generally around 40 %, with 60 % in specialized addiction centers with urinary testing and supervision [4, 5]. In studies performed in our area, observed retention rates were similar [13]. Using reimbursement data from the French Health Insurance system at the regional level, we compared retention rate of patients newly treated by buprenorphine according to performing or not urinary testing [27]. In this study including 1,507 subjects followed-up over 30 months, the retention rate in patients with urinary testing was significantly better than the reference group, with an adjusted Hazard Ratio of 0.55 (95 % CI: 0.38–0.80).

Thus, considering a retention rate in the reference group of 36 %, and an expected retention rate of 50 % in the intervention group, if mean cluster size (m) = 2, α risk = 0.05 and β risk = 0.20, the theoretical formula of Hayes and Moulton gives 100 clusters by group, i.e. 100 GPs in each group, corresponding to 200 patients in each group, i.e. 400 patients in all [45].

Recruiting 2 patients by GPs over a period of 18 months seems realistic, even if these GPs are not working in an addiction specialized network. Hypothesizing that the expected retention rate will be 50 % in the intervention group is very conservative. Actually, with an expected retention rate of 60 % (as observed in our previous study) or with an expected relative risk of 0.3-0.4 in favour of the intervention group (as observed in the McCowan study [28], with a benefit of performing urinary testing -whatever the results- on mortality in patients treated by methadone in UK). With this retention rate, only 34 clusters should be needed, corresponding to 34 GPs in each group, 68 in the all sample, and consecutively 136 patients. This hypothesis should be probably optimistic but not completely unrealistic.

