### Statistical analysis

Patients, will be analyzed according to the intervention assigned to their GPs, whether being exposed to OS-UDS during their participation or not, in accordance with the intention-to-treat principle.

For patients followed up until the end of the study, the retention rate will be the percentage of patients still under OMT (complete data). For loss of follow up patients, an intention to treat approach will be used and loss of follow will be analyzed as failure.

A description of the baseline characteristics of the group will be performed, comprising mean ± SD for continuous variables and frequency and percentages for qualitative variables. Baseline characteristics and secondary outcomes will be compared among groups using the Chi2 test of independency or Fisher test for categorical variables and the Student t test or the Wilcoxon test for continuous variables. A significance threshold of 5 % will be applied for all the statistical analyses.

Retention at 6 months will be computed as an individual binary variable, and will be analyzed using mixed effect logistic regression, including GPs as a random effect parameter. Potential confounders or explanatory variables at individual and cluster level will be included. An alternative way for analysis would consist in applying generalized estimating equation (GEE). These models are appropriate in the study design as the number of cluster will be higher than 15 [43].

Univariate analyses on baseline variables as potential predictors for success or failure of OMT maintenance will be performed using Chi-square statistics for categorical and Student t-test for continuous data. Variables with a P-value of <0.2 after univariate analysis will be entered into a multivariate logistic regression model. Crude and adjusted Odds Ratio (OR) and their confidence intervals will be estimated. The main analysis will be completed by univariate and multivariate clustered survival analyses.

Analyses will be performed using the SAS ® 9.3 software (SAS Institute Inc., Cary, NC, USA).

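### Diverted use counts as non-retention on the unblinded GP's judgement, and only one arm has test kits, so primary failures may be ascertained differently by arm

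*Protocol article*

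**What the plan says.** The Primary outcome section defines retention as being on medically prescribed opiate maintenance treatment (OMT) at 6 months, "assessed by the general practitioner at the end of the follow-up". It then lists exceptions. One is that in case of "diverted use of drug (intravenous or nasal route or illegal acquisition of the OMT drug), the patient will be considered as not retained". A patient with a current prescription can therefore be scored a failure because of what the GP knows about how the drug is used or obtained.

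The GP is the unit of randomization. In the intervention arm the GP is trained and supplied with kits for buprenorphine, EDDP (the methadone metabolite), opiates and cocaine. One test is required, before the first prescription. After that, "GPs will be let free to perform OS-UDS for the follow-up if they judge it necessary". The Controlled group section excludes on-site tests but allows any other biological test, including laboratory testing, and expects such testing in 1 to 3 % of cases.

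SNIIRAM records will be linked to complete prescription and follow-up information, but "Data collected will not be included in the main analysis".

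**The concern.** Most of the retention definition rests on facts that do not depend on testing, such as whether a prescription exists and whether the patient attends. The diversion clause is different. It counts only when the GP comes to know of it, and the intervention is meant to improve what the GP knows about drug use. The Background section itself argues that self-report and clinical judgement underestimate consumption, and that GPs who test mainly report a better dialogue with the patient. If testing or the dialogue around it brings more diversion to light, the intervention arm accumulates failures that would go unrecorded in the control arm.

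The same GP delivers the intervention and scores the outcome without blinding, so a favourable reading of doubtful cases is also possible. In either case part of the arm difference would reflect ascertainment rather than retention. No analysis of a single recorded yes/no outcome can separate the two afterwards.

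**Working it through.** **Inputs from the Sample size calculation section.** Rates: "considering a retention rate in the reference group of 36 %, and an expected retention rate of 50 % in the intervention group". Errors: "α risk = 0.05 and β risk = 0.20". Clustering: "intra-cluster correlation coefficient (CCI = 2.79 %) and the mean cluster size (m = 2), giving an inflation factor (IF = 1.03". Planned size: 100 GPs and 200 patients per group. The Statistical analysis section states a 5 % threshold without sidedness. I take it as two-sided, which reproduces the plan's figure.

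**The plan's own figure.** Hayes and Moulton formula for unmatched clusters, in its intra-cluster-correlation form:

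c = 1 + (1.960 + 0.842)² × [p0(1−p0) + p1(1−p1)] × [1 + (m−1)ICC] / [m(p1−p0)²]

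= 1 + 7.849 × (0.2304 + 0.2500) × 1.0279 / (2 × 0.0196) = 99.9, so 100 clusters per group, as stated. The sample size is not in dispute.

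**Power at the planned size.** The effective n per group is 200 / 1.0279 = 194.6. With a pooled standard error s0 under the null and an unpooled s1 under the alternative:

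power = Φ[(p1 − p0 − 1.960 × s0) / s1]

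For 36 % vs 50 %: s0 = 0.0502, s1 = 0.0497, power = 80 %.

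**Extra diversion failures in the intervention arm (assumed).** Let d be the share of truly retained intervention patients who are additionally classed as diverted because of testing. Observed retention is 0.50 × (1 − d), against 36 % in control.

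| d | Observed retention, intervention | Power |
|---|---|---|
| 0 | 50.0 % | 80 % |
| 2 % | 49.0 % | 74 % |
| 5 % | 47.5 % | 63 % |
| 10 % | 45.0 % | 44 % |

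**No true effect (both 36 %), bias in either direction (assumed).**
- Extra detection with d = 5 %: 34.2 % vs 36 %, two-sided rejection rate 6.6 %.
- Extra detection with d = 10 %: 32.4 % vs 36 %, rejection rate 11.6 %, nearly all towards apparent harm.
- Leniency, with 5 % of non-retained intervention patients scored as retained: 0.36 + 0.64 × 0.05 = 39.2 % vs 36 %, rejection rate 10.0 %, mostly towards apparent benefit.

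**A two-parameter version (assumed).** Let a share v of patients on prescription divert, and let the GP detect a share s of them. Measured retention is p × (1 − v × s).
- v = 20 %, s = 60 % vs 20 %: 0.50 × 0.88 = 44.0 % vs 0.36 × 0.96 = 34.6 %, power 48 %.
- v = 10 %, s = 25 % vs 20 %: 0.50 × 0.975 = 48.8 % vs 0.36 × 0.98 = 35.3 %, power about 77 to 78 %, depending on whether the null standard error is pooled.

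**What a test can show about the clause.**

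| Element of the clause | Can the kit show it? |
|---|---|
| Intravenous or nasal route | No; buprenorphine is positive whatever the route |
| Illegally obtained buprenorphine | No; not distinguishable from prescribed drug |
| Illegally obtained methadone | Suggested by a positive EDDP result with no known prescription |
| Any of these, through disclosure | Possibly, if the test prompts the conversation |

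A negative buprenorphine test suggests non-intake. The clause does not list that, and the article treats adherence as a secondary outcome.

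**The case against.** The strongest reply is that the kit is a poor detector of diversion as the article defines it. It shows neither route nor the source of buprenorphine, and the only required test comes too early to reflect any drug prescribed in the trial. Later tests are at the GP's discretion, at a rate the article does not give. Control GPs may order laboratory tests. All of this stands. It limits the mechanism to unexplained methadone and to disclosure, and it makes differential detection a possibility, not an established fact. The control-arm allowance narrows the contrast only slightly, since 1 to 3 % testing is expected there.

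The magnitudes also rest wholly on assumed rates, and a small detection gap leaves power close to the planned 80 %. That stands too.

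Keeping SNIIRAM out of the main analysis is defensible. Matching is probabilistic, with about 80 % matched in the study the article cites, and the data cannot show route or illegal acquisition. The sentence excludes them from the main analysis only, so a sensitivity analysis is already compatible with it.

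Scoring patients lost to the GP, or treated by an unconnected prescriber, as failures is one rule for both arms and is not detection by the kit. Retention in a context of medical care is a deliberate construct, and blinding the GP is not feasible in this design.

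None of this removes the core problem. A failure criterion that depends on the GP's knowledge is scored by an unblinded GP whose means of knowing differ by arm, and the article describes no safeguard.

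**Conclusion.** The point holds as a risk of allocation-dependent ascertainment of the primary outcome, and it should be fixed. Its direction is not determined: added detection works against the intervention, leniency works for it. Its size is unknown. Under the assumption that 2 to 10 % of retained intervention patients are additionally reclassified, power falls from 80 % to between 74 % and 44 %.

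A reader might infer more: that the kits reveal diversion, that failures therefore are detected differently in the two arms, and that the primary comparison no longer answers its question. The documents do not support that. The four-analyte test bears directly on only one element of the clause, follow-up testing is optional and unquantified, and the other failure criteria (such as the rule of more than 56 days without a visit) depend less on testing. Nor do the documents show that the primary outcome must be redefined or that SNIIRAM data should replace the GP's assessment.

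**What to change.** 1. Record two separate items at 6 months (± 14 days) in both arms: (a) whether an OMT prescription was in force, and (b) diverted use. Rate (b) by written criteria identical in both arms, and state that on-site test results may not be used for it.
2. Keep the primary definition if the construct is wanted, but prespecify an analysis of prescription-based retention without the diversion component, reported alongside the primary analysis.
3. Prespecify a supportive sensitivity analysis that reclassifies retention by SNIIRAM dispensing in the same window, including patients lost to the GP or followed by an unconnected prescriber. The Cross-link data sentence can stay as it is.

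The cost is some wording on the follow-up questionnaire and two extra analyses, one on data already being linked. There are limits. About 20 % of patients may not match in SNIIRAM, and those data are silent on route and illegal acquisition. Disclosure prompted by testing can still influence item (b), and this is why retention without that item has to be reported as well. The Trial status section describes the study as ready to include, so at that stage the change can precede any outcome recording.

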#### Secondary outcomes

The secondary judgment criteria will be the adherence to buprenorphine associated psychoactive substances use, and acceptability of OS-UDS reported by the patient, the GP.

We will specifically collect for both groups: characteristics of buprenorphine utilization (dose, duration), exposure to opiate or other illegal substances (heroin, morphine, cannabis, cocaine, benzodiazepines, amphetamines, other…) during the follow-up (self-reported during medical examination and/or biologically assessed); for the intervention group: number of OS-UDS performed by GP and by patient acceptability reported by the patient and by the GP (self-reported questionnaires).

#### Cross-link data

To ensure completeness in prescription drug records, significant medical event and death occurring during follow up, additional information on medical care will also be obtained through the database of the health insurance scheme. A query into the information system from the national health insurance scheme database (SNIIRAM) and national mortality registry will be done to complete follow-up [39]. Patients will be matched thanks to a probabilistic match [40]. In a recent study, around 80 % of patients had been matched between general practice data and health insurance scheme data [41]. Data collected will not be included in the main analysis.

### Sample size calculation

Comparisons between groups will be performed taking into account clustering which the unity will be the GP. Thus the sample size must be corrected by an inflation factor according to guidelines on clustered analyses [42–45]. According to the results of a previous study performed by our group on patients initiating buprenorphine in ambulatory care in the Midi-Pyrénées area [27], we were able to identify clusters of GPs and calculated the intra-cluster correlation coefficient (CCI = 2.79 %) and the mean cluster size (m = 2), giving an inflation factor (IF = 1.03).

According to the literature, the retention rate with buprenorphine at 6 months is generally around 40 %, with 60 % in specialized addiction centers with urinary testing and supervision [4, 5]. In studies performed in our area, observed retention rates were similar [13]. Using reimbursement data from the French Health Insurance system at the regional level, we compared retention rate of patients newly treated by buprenorphine according to performing or not urinary testing [27]. In this study including 1,507 subjects followed-up over 30 months, the retention rate in patients with urinary testing was significantly better than the reference group, with an adjusted Hazard Ratio of 0.55 (95 % CI: 0.38–0.80).

Thus, considering a retention rate in the reference group of 36 %, and an expected retention rate of 50 % in the intervention group, if mean cluster size (m) = 2, α risk = 0.05 and β risk = 0.20, the theoretical formula of Hayes and Moulton gives 100 clusters by group, i.e. 100 GPs in each group, corresponding to 200 patients in each group, i.e. 400 patients in all [45].

Recruiting 2 patients by GPs over a period of 18 months seems realistic, even if these GPs are not working in an addiction specialized network. Hypothesizing that the expected retention rate will be 50 % in the intervention group is very conservative. Actually, with an expected retention rate of 60 % (as observed in our previous study) or with an expected relative risk of 0.3-0.4 in favour of the intervention group (as observed in the McCowan study [28], with a benefit of performing urinary testing -whatever the results- on mortality in patients treated by methadone in UK). With this retention rate, only 34 clusters should be needed, corresponding to 34 GPs in each group, 68 in the all sample, and consecutively 136 patients. This hypothesis should be probably optimistic but not completely unrealistic.

This strategy will allow to overcome the proper effect of each GP, to get enough clusters for the analysis and to regroup clusters (on the basis of the same geographic area (in French “Bassins de santé”) giving a sufficient number of individuals in each cluster (5 subjects).

The Fig. 1 summarizes the design of the study.

**Fig. 1 Fig1:**
[figure not shown]
Design of the ESUB-MG pragmatic randomized controlled trial

### Statistical analysis

Patients, will be analyzed according to the intervention assigned to their GPs, whether being exposed to OS-UDS during their participation or not, in accordance with the intention-to-treat principle.

For patients followed up until the end of the study, the retention rate will be the percentage of patients still under OMT (complete data). For loss of follow up patients, an intention to treat approach will be used and loss of follow will be analyzed as failure.

A description of the baseline characteristics of the group will be performed, comprising mean ± SD for continuous variables and frequency and percentages for qualitative variables. Baseline characteristics and secondary outcomes will be compared among groups using the Chi2 test of independency or Fisher test for categorical variables and the Student t test or the Wilcoxon test for continuous variables. A significance threshold of 5 % will be applied for all the statistical analyses.

Retention at 6 months will be computed as an individual binary variable, and will be analyzed using mixed effect logistic regression, including GPs as a random effect parameter. Potential confounders or explanatory variables at individual and cluster level will be included. An alternative way for analysis would consist in applying generalized estimating equation (GEE). These models are appropriate in the study design as the number of cluster will be higher than 15 [43].

Univariate analyses on baseline variables as potential predictors for success or failure of OMT maintenance will be performed using Chi-square statistics for categorical and Student t-test for continuous data. Variables with a P-value of <0.2 after univariate analysis will be entered into a multivariate logistic regression model. Crude and adjusted Odds Ratio (OR) and their confidence intervals will be estimated. The main analysis will be completed by univariate and multivariate clustered survival analyses.

Analyses will be performed using the SAS ® 9.3 software (SAS Institute Inc., Cary, NC, USA).

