## Methods/Design

### Study design

The ESUB-MG study is a pragmatic, cluster randomized controlled trial design. Clustering is at the level of the GP. A cluster design is needed as the intervention concerns the GP and as the evaluation concerns the patient. Furthermore, patients of a same GP are more correlated than patients of different GPs.

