### Randomization

Randomization will be undertaken at the cluster (GP) level. Based on the procedure allocated to GP, all patients within a cluster will be assigned to either intervention or control group.

Randomization of participating GP will be performed after GP’s approval and collecting complete questionnaire including basic demographic information and their location. The randomization list will be generated by an independent biostatistician in the clinical research methodological support unit (Unité de Soutien Méthodologique à la Recherche Clinique USMR) of the University hospital (Centre Hospitalier Universitaire CHU) of Toulouse, France. Clusters will not be randomized all at once (first patients inclusion need to begin whereas GPs’ recruitment will be on-going), thus the allocation for each consecutive participating GP will be obtained from the USMR through a specific website. To avoid contamination bias, no more than one GP could be included in a given medical practice.

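### Secondary outcomes compared between arms are tested as if patients were independent, although GPs are randomised and the plan says group comparisons allow for clustering

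*Protocol article*

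**What the plan says.** The protocol article sets out the clustering in three places. Under Randomization: "Randomization will be undertaken at the cluster (GP) level". Under Study design it gives as one reason for the design that "patients of a same GP are more correlated than patients of different GPs". The Sample size calculation section opens with "Comparisons between groups will be performed taking into account clustering which the unity will be the GP", and the sentence is not limited to the primary outcome.

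The Statistical analysis section follows this for retention at 6 months, which "will be analyzed using mixed effect logistic regression, including GPs as a random effect parameter", with GEE as an alternative. The supplementary survival analyses are also described as clustered.

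For secondary outcomes the same section names different methods: "Baseline characteristics and secondary outcomes will be compared among groups using the Chi2 test of independency or Fisher test for categorical variables". Continuous outcomes get an ordinary t or rank-sum comparison in the same way. On the level of testing it adds: "A significance threshold of 5 % will be applied for all the statistical analyses". No adjustment for GP is attached to these tests there or elsewhere in the article.

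The Secondary outcomes section separates what is collected in each arm. Buprenorphine utilisation (dose, duration) and exposure to opiates and other substances are collected in both groups. The number of on-site tests and acceptability to patient and GP are collected in the intervention group only.

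**The concern.** The chi-square, Fisher, Student t and Wilcoxon tests all take the patient as an independent unit. Here treatment is assigned to the GP, so every patient of a GP is in the same arm and correlation within a GP adds to the variance of the between-arm difference. An ordinary test leaves that component out. Its standard error is then too small, and a nominal 5 % test rejects too often.

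This is a method the article states, not a detail left for a later document, and an analysis plan written from this text would carry it forward. The outcomes affected are not incidental: the Discussion presents an effect on patients' adherence as one of the important things the trial could show. There is also some reason to expect a GP effect on what is recorded. Substance use is reported at consultation and/or measured biologically, follow-up testing is at the GP's discretion, and no visits are scheduled. That makes a GP effect plausible, but the article gives no figure for it.

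**Working it through.** **Inputs from the article.** Mean cluster size m = 2, ICC = 0.0279, inflation factor 1.03, retention 36 % against 50 %, β = 0.20 and 100 GPs per group (Sample size calculation); α = 0.05 (Statistical analysis; two-sided assumed, since sidedness is not stated); 1 to 10 patients per GP (Abstract).

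**Step 1: reproduce the plan's figures.**

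- Design effect DE = 1 + (m − 1) × ICC = 1 + 1 × 0.0279 = 1.0279, which rounds to the stated 1.03.
- Clusters per group = 1 + (1.96 + 0.84)² × [(0.36 × 0.64 + 0.50 × 0.50) × DE / m] / 0.14². With unrounded normal quantiles this is 1 + 98.87 = 99.87, matching the stated 100.

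The plan's clustering inputs are therefore clear and can be applied to the secondary tests.

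**Step 2: true error of an unadjusted test.** With no treatment effect, the ordinary test statistic has variance of about DE instead of 1. The true two-sided error is 2 × [1 − Φ(1.96 / √DE)].

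At the plan's values: √1.0279 = 1.0139 and 1.96 / 1.0139 = 1.933, so the true error is 5.32 %.

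**Step 3: other ICCs at m = 2.** The ICC of 0.0279 was calculated in an earlier study of patients starting buprenorphine. The article gives no ICC for adherence or substance use, so the values below the first row are assumptions.

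| ICC | DE | True error |
|---|---|---|
| 0.0279 (plan) | 1.0279 | 5.3 % |
| 0.05 | 1.05 | 5.6 % |
| 0.10 | 1.10 | 6.2 % |
| 0.20 | 1.20 | 7.4 % |
| 0.30 | 1.30 | 8.6 % |

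**Step 4: uneven clusters.** With mean size 2 and a coefficient of variation (CV) of cluster size, DE = 1 + [(1 + CV²) × 2 − 1] × ICC. The article gives no CV. For an assumed CV of 0.8:

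| ICC | DE | True error |
|---|---|---|
| 0.0279 (plan) | 1.0636 | 5.7 % |
| 0.10 (assumed) | 1.228 | 7.7 % |
| 0.20 (assumed) | 1.456 | 10.4 % |

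Uneven clusters alone change little at the plan's ICC. A material excess needs a larger ICC as well.

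**The case against.** The strongest reply is that the effect is negligible on the only documented inputs: 5.3 % instead of 5 %. That stands, and anything larger rests on an ICC or a cluster-size spread that the article does not give. The spread is itself uncertain. The Abstract allows 1 to 10 patients per GP, whereas Patients' recruitment asks for at least two, and a mean of two with a minimum of two leaves no variation at all.

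A second reply is that the sentence on clustering sits in the sample size section and leads straight into the inflation factor, so it may be meant only for the powered comparison. That softens the contradiction but does not remove the point. The tests remain wrong for a GP-randomised design whose within-GP correlation the article itself acknowledges.

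A reader might also infer more than the documents support:

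- *That every secondary outcome is affected.* Acceptability and the number of on-site tests are collected in the intervention arm only, so no between-arm test arises for them.
- *That the planned confidence intervals are too narrow.* Intervals are announced only for the retention analysis ("Crude and adjusted Odds Ratio (OR) and their confidence intervals will be estimated"), and none for secondary outcomes. The remark would apply only to intervals later derived from the same unadjusted methods.
- *That baseline tests are uninformative because GPs were randomised and patients recruited afterwards.* Recruitment after allocation means that imbalance can be real, so this reasoning fails. The baseline description is not part of the point.
- *That the error is 8 % to 14 %.* Those values need an ICC of 0.10 to 0.30 and a cluster-size CV of 0.9 together, and neither is in the article. A CV of 0.9 at the plan's ICC gives DE = 1 + 2.62 × 0.0279 = 1.073 and about 5.9 %.

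**Conclusion.** The point holds for the secondary outcomes compared between arms, namely buprenorphine adherence or utilisation and associated psychoactive substance use. The stated tests ignore the unit of randomisation and do not fit the article's own statement on group comparisons. The direction of the error follows from positive within-GP correlation, which the article accepts.

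The documented size is small, a true error of about 5.3 %. It would be about 6 % to 9 % at a mean cluster size of 2 if the ICC for these outcomes were 0.10 to 0.30, and higher if cluster sizes are also uneven. Both conditions are assumptions. The primary retention analysis already includes the GP effect and is not in question. This should be corrected because it is a stated error that is easy to put right, not because it threatens the trial's main conclusion.

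**What to change.** In the Statistical analysis section, replace the ordinary tests for between-arm secondary outcomes with the approach already chosen for retention: a mixed logistic model (categorical) or mixed linear model (continuous) with a GP random intercept, or GEE clustered on GP. Where a continuous outcome is too skewed for a linear model, compare GP-level summaries or use a cluster-adjusted test. State that the intervention-arm-only outcomes are described and not compared. This brings the section into line with the statement under Sample size calculation.

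The change is to analysis wording only; data collection, sample size and conduct stay as they are. P-values become slightly larger, and any intervals reported become wider by a factor of √DE: about 1.4 % at the plan's values (√1.0279 = 1.014), and about 14 % at the highest ICC assumed above with m = 2 (√1.30 = 1.140).
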